# 2. Objectives of the study

*Overall objective:* to demonstrate the "Value Chain" concept in a contractual agreement linking the Laiterie du Berger and milk producers in the area of Richard Toll, Senegal.

*Specific objectives:* to compare the results of a micronutrient-fortified Thiakry intervention with a control group, specifically concerning:
- Increasing the volume of milk and the frequency of collection during the dry season
- Reducing the prevalence of anemia among children aged 2 to 5 years

3. Criteria for assessment

*Main outcome of the intervention:* proportion of herders who have reached their contract objective defined in the beginning of study, in terms of volume and collection frequency for milk over the duration of the study

*Main outcome for the "Nutrition" component:* proportion of children 2 to 5 years presentingsevere, moderate, and mild anemia (defined thresholds respectively are <7, between 7 and 9.9, and between 10 and 10.9 g/dl of hemoglobin).

*Secondary outcome of the "Nutrition" component (at 6 and 12 months of follow-up):*- Mean level of hemoglobin (in g/dl)
- Proportion of children 2 to 5 suffering from stunting (Height-for-Age Indices <-2SD)
- Proportion of children 2 to 5 years suffering from acute malnutrition (Weight-for-Height Indices <-2 SD)
- Proportion of children 2 to 5 years who are underweight (Weight-for-Age Indices <-2 SD)

- Household food consumption

- Children’s dietary diversity

*Definitions:*

- Mild anemia in children: level of hemoglobin between 10 and 10.9 g/dl of blood

- Moderate anemia in children: level of hemoglobin between 7 and 9.9 g/dl of blood

- Severe anemia in children: level of hemoglobin less than 7 g/dl of blood

- Stunting (Height-for-Age Indices <-2SD)

- Acute malnutrition or wasting (Weight-for-Height Indices <-2 SD)

- Underweight (Weight-for-Age Indices <-2 SD)

# 4. Location of the study

LDB is located in the area of Richard Toll, along the Senegal River Delta in the administrative department of Dagana. Collection routes are located in the Dieri and in the Walo (flood zone near the river, where rice is commonly grown). The herding in the Walo is of a more sedentary/agro-pastoral nature whereas the herding in the Dieri is generally pastoral with transhumance (Parisse, 2011).

[figure not shown]

*Figure 1: Collection routes around Richard Toll, Senegal*

# 5. Study design

The study will be randomized and single-blind. Of the 4 collection routes (Figure 1), 500 milk containers are collected every day, corresponding to an average of 2 households of herders per container. Randomization will be made at the level of household concessions, with certain concessions receiving fortified Thiakry and others making up the control group.

# 6. Subject characteristics

# *Selection Criteria:*

- All households of herders supplying milk to the Laiterie du Berger and having children 2 to 5 years in the household, who agree to regularly provide milk to LDB

- Signature of an agreement to participate in the study by the head of household and his/her spouse(s) and signature of the informed consent by the mother of the children

*Non-inclusion criteria:*

- Refusal to participate in the study

*Exclusion criteria:*

- Subjects may discontinue participation in the study at any moment

# 7. Number of subjects

Calculating the number of required subjects is based on the main assessment criterion of the nutrition component of the study: anemia. Considering that the consumption of fortified Thiakry by children has the potential to reduce the prevalence of anemia by 15%, from an average prevalence of 75% to 60%, the number of required subjects is 165 subjects per group, totally 330 subjects, with 80% power and 5% alpha (unilateral test). This is a cluster trial, with the the concession as the randomization unit. We have therefore taken into account an intracluster correlation coefficient of 0.3, which gives an estimate of 430 children aged 2-5 years required. Estimating an attrition of 20%, we would need to recruit 550 children. Moreover, it is likely that not all households will participate in the study (largely due to the phenomenon of transhumance in the area) and that not all households will achieve their objective in terms of milk production in order to obtain the incentive. Among children in the group receiving the fortified Thiakry, there is no guarantee that all of the product will be consumed and at the necessary frequency (every day) to see a reduction of anemia. We therefore estimate that another 20% of the number of households may ineligible for analysis, bringing the total number of subjects required to 660 children. As the number of households of the area is approximately 700, with an average of 2 children in the age group of interest per household, we are confident that we will be able to access the necessary number of children.

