**11.2. Methods and data analysis models**

The impact of the intervention will be analyzed using the "difference in differences" method: the difference in the prevalence of anemia for children 2 to 5 years or the difference of average hemoglobin levels, i) between the treatment and the control group and ii) between the beginning and the end of the intervention. It will be possible to use a propensity score, determined from the baseline characteristics, in order to check the comparability between groups and, if necessary, to use the score as an adjustment factor. All tests performed will be unilateral, with a 95% confidence interval. The analysis will be performed using STATA 12.0 (Stata statistical software, Stata Corporation, College Station, Texas USA).

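### The 165 per group does not follow from a one-sided 5% test at 80% power, and the blanket one-sided rule in section 11.2 is not reconciled with its 95% interval

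*Protocol*

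**What the plan says.** Protocol section 7 (Number of subjects) bases the sample size on anemia, the main outcome of the nutrition component. It supposes that fortified Thiakry could "reduce the prevalence of anemia by 15%, from an average prevalence of 75% to 60"%, and concludes that "the number of required subjects is 165 subjects per group, totally 330 subjects, with 80% power and 5% alpha (unilateral test"). It then inflates for clustering (an "intracluster correlation coefficient of 0.3, which gives an estimate of 430 children aged 2-5 years required"), for attrition (550) and for further ineligibility (660).

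Protocol section 11.2 (Methods and data analysis models) sets one rule for the whole analysis: "All tests performed will be unilateral, with a 95% confidence interval". It does not say in which direction the tests point, why one-sided testing was chosen, or whether the interval is one- or two-sided. The only significance level in the document is the 5% of section 7; nowhere is a one-sided 2.5% level set.

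**The concern.** There are two linked problems.

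First, section 7 gives everything needed to check 165 (two prevalences, power, alpha and sidedness), and the number is clearly larger than a one-sided 5% test at 80% power requires. Either the sidedness or the power is misreported, so a reader cannot tell which error rates the trial was designed to have.

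Second, the one-sided label is carried into the analysis as a universal rule. A one-sided 5% test does not correspond to a conventional two-sided 95% interval, which corresponds to one-sided 2.5%. For a borderline result the test and the interval could therefore disagree, and the plan does not say which decides. A test pointed only at benefit also cannot declare an effect in the wrong direction significant. That matters for the nutrition outcomes of section 3 (stunting, wasting, underweight, household food consumption, dietary diversity), for which the protocol gives no reason to rule out a move in either direction.

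**Working it through.** **Inputs**, all from section 7: p₁ = 0.75, p₂ = 0.60, difference d = 0.15, power 80%, alpha 5%, equal groups. Mean prevalence p̄ = (0.75 + 0.60)/2 = 0.675.

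**Formula** (pooled-variance comparison of two proportions, per group):

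n = [z_α √(2p̄(1−p̄)) + z_β √(p₁(1−p₁) + p₂(1−p₂))]² / d²

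with √(2 × 0.675 × 0.325) = √0.43875 = 0.6624 and √(0.1875 + 0.2400) = √0.4275 = 0.6538.

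Continuity correction: n_c = (n/4) × [1 + √(1 + 4/(n d))]².

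**Which inputs give 165?**

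| Test and power | Numerator before squaring | n | n with correction |
|---|---|---|---|
| Two-sided 5%, 80% | 1.960 × 0.6624 + 0.8416 × 0.6538 = 1.8485 | 151.9 → 152 | **164.9 → 165** |
| One-sided 5%, 80% (as stated) | 1.645 × 0.6624 + 0.8416 × 0.6538 = 1.6398 | 119.5 → 120 | 132.5 → 133 |
| One-sided 5%, 90% | 1.645 × 0.6624 + 1.2816 × 0.6538 = 1.9274 | 165.1 → 166 | 178.2 → 179 |

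Other common variants do not rescue the stated inputs. At one-sided 5% and 80% power, the unpooled formula gives 118, the simple pooled formula 121 and the arcsine formula 120. At two-sided 5% and 80% power, the same three give 150, 154 and 152. With the stated 80% power, only the two-sided, continuity-corrected calculation gives 165 exactly.

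**Power at 165 per group**, before clustering:

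| Test | Pooled formula | Continuity-corrected | Fisher exact |
|---|---|---|---|
| One-sided 5% | 90.0% | 87.7% | 87.9% |
| Two-sided 5% | 83.2% | 80.0% | 80.5% |

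For the pooled one-sided case: (0.15 × √165 − 1.645 × 0.6624)/0.6538 = 1.28, and Φ(1.28) = 0.90.

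**Later steps.** With two children per cluster and ICC 0.3 the design effect is 1 + (2 − 1) × 0.3 = 1.3, and 330 × 1.3 = 429, in line with the stated 430. The 550 and 660 build on that figure, so correcting the sidedness label changes none of them.

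**Test against interval.** A two-sided 95% interval excludes no effect on the beneficial side exactly when the one-sided p is below 0.025. A one-sided 5% test rejects when p is below 0.05. For 0.025 < p < 0.05 the test is significant and the interval includes no effect. Outside that band the two agree about benefit.

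**The case against.** Several counter-arguments carry weight.

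- *The sidedness label may not be the wrong input.* One-sided 5% at 90% power without correction gives 165.1, which is 165 by ordinary rounding. One-sided testing appears in both section 7 and section 11.2, so it may be deliberate, and the protocol never mentions a continuity correction. This stands as far as it goes: a wrong label is the better fit, because it keeps both the stated power and the stated number, but it is not proven. On either reading one stated input is wrong.

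- *A reader might infer that the false-positive rate is doubled.* The documents do not support that without qualification. The declared level is 5% one-sided, and the type I error per test stays at that 5%. Only the chance of a false claim of benefit doubles, from 2.5% to 5%, and only against a two-sided 5% standard that the protocol does not state.

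- *A reader might infer a flat contradiction with the interval.* Section 11.2 does not specify the kind of interval, and a one-sided 95% bound would match a one-sided 5% test. The clash depends on the usual two-sided reading and is confined to the band shown above.

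- *A reader might infer that harm cannot be shown at all.* That goes too far. Section 11.2 estimates difference-in-differences effects with an interval, and a two-sided interval could display an adverse effect. What a test towards benefit cannot do is declare it significant.

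- *Two-sided testing costs power, and the margin may be thinner than it looks.* The design effect of 1.3 uses two children per cluster, but section 7 gives two as the average per household, while the concession is randomized. As an illustration, assume 660 recruited, both 20% losses removed (660 × 0.8 × 0.8 = 422) and ICC 0.3. Pooled-formula power, one-sided and two-sided, is then 90% and 83% with two children per concession, 83% and 74% with three, and 77% and 67% with four. This is a fair caution, but it concerns the assumed cluster size, which deserves its own check; it does not make 165 follow from the stated inputs.

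**Conclusion.** The point holds in a limited form. On section 7's own inputs the requirement is 120 per group (133 corrected), not 165, and 165 gives the stated test about 88–90% power rather than 80%. The most economical explanation is a two-sided, continuity-corrected calculation labelled one-sided; misreported power is possible, and only the sponsor can settle it. The mismatch does not leave the trial too small for a one-sided test at this step.

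The universal one-sided rule in section 11.2 is badly fixed as written: it gives no direction and no reason, and pairs the tests with an interval of unstated type. On the usual two-sided reading, a one-sided p between 0.025 and 0.05 for anemia could be claimed as an effect that the reported interval does not support. This conclusion rests on alpha being the 5% of section 7 and on the interval being two-sided.

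**What to change.** Ask the sponsor to confirm how 165 was obtained. Then:

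- **Section 7:** describe the calculation as a two-sided 5% test with 80% power and continuity correction. The 165 and 330 stand, and 430, 550 and 660 need no change on this account.
- **Section 11.2:** replace the sentence on sidedness with: All tests will be two-sided at 5%, with two-sided 95% confidence intervals.

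The cost is a change of wording in two places and some power: about 80–83% instead of 88–90% at 165 per group before clustering, which still meets the stated 80%. No extra children are needed relative to the stated size. The choice should be recorded before outcome data are analysed, since sidedness chosen afterwards would not be credible.

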# 8. Conditions of the lottery

The two groups will be chosen by lottery at the first information-sharing meeting. The draw will define the households receiving free fortified Thiakry for all children aged 2 to 5 years within their household (treatment group) and the households not receiving fortified Thiakry during the study (control group), who will receive in kind compensation at the end of the study as thanks for their participation.

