**10.4.** **Intervention**

The distribution phase of the incentive will last 6 months, from January 2013 to July 2013. The incentive of fortified Thiakry will be distributed daily by the milk collectors. Participants in the study who are part of the treatment group will have the daily opportunity to buy fortified Thiakry directly from the milk collection truck. During the study, if a herder responsible for the milk container has committed to providing a certain quantity of milk daily to LDB and does not honor their commitment one or two days in the same week, they will receive a warning (if they are in the treatment group). If the herder does not provide milk for 3 or more days in the week and is in the treatment group, they will not receive the fortified Thiakry the following week.

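### The step from 330 to 430 children assumes 2 per cluster, which is the household figure although concessions are said to be randomised, and section 11 specifies its analyses without any allowance for the cluster

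*Protocol*

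**What the plan says.** Section 7 of the protocol sizes the trial on anaemia in children: the product is expected to "reduce the prevalence of anemia by 15%, from an average prevalence of 75% to 60" per cent. It states that "the number of required subjects is 165 subjects per group, totally 330 subjects", "with 80% power and 5% alpha (unilateral test"). It then calls the study a cluster trial with the concession as the randomisation unit and applies an "intracluster correlation coefficient of 0.3, which gives an estimate of 430 children aged 2-5 years required". No cluster size is given with that step. The only count of children is an average of 2 in the age group per household, at the end of the same section.

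The unit is described differently elsewhere:

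- Section 5 reports collection by milk container, "corresponding to an average of 2 households of herders per container. Randomization will be made at the level of household concessions".
- Section 8 says: "The draw will define the households receiving free fortified Thiakry for all children aged 2 to 5 years within their household". Section 10.1 also describes the lottery in terms of households.

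Sections 11.1 and 11.2 name a comparison of proportions between groups, an adjusted multivariable analysis, a difference-in-differences estimate and an optional propensity score. They also give the software and the sidedness: "All tests performed will be unilateral, with a 95% confidence interval". Neither mentions the concession, the household as a cluster, robust standard errors or a random effect.

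**The concern.** Two things do not fit together.

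First, a design effect must use the number of children in the unit that is randomised. The one used here corresponds to a household, while the same paragraph names the concession. If a concession holds several households, the allowance for clustering is too small for the stated design.

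Second, the protocol judges correlation within clusters strong enough to add 100 children to the sample, yet it sets out its analyses without it. If the tests were run as written, standard errors would be too small, confidence intervals too narrow, and false-positive findings more frequent than 5%. This second problem does not depend on concession size, because with an average of 2 children per household it arises even if single households are drawn.

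**Working it through.** **Inputs.** From section 7: prevalence 75% and 60% (difference 0.15), one-sided 5% alpha, 80% power, 165 per group (330 in total), ICC 0.3, 430 children after clustering, 2 children per household. Children per concession is not in the document, so cluster sizes m = 3 and m = 4 are assumptions used to show a range.

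**Step 1: reproduce 430.** Design effect DE = 1 + (m − 1) × 0.3. At m = 2, DE = 1.3 and 330 × 1.3 = 429, which rounds to 430. Working backwards, m = 1 + (430/330 − 1)/0.3 = 2.01. The figure reproduces, with 2 children per cluster.

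**Step 2: the same method at other cluster sizes.** m = 3: 330 × 1.6 = 528. m = 4: 330 × 1.9 = 627. All are before attrition.

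**Step 3: check the starting 165.** The usual formula for two proportions is n = [z_α √(2p̄(1 − p̄)) + z_β √(p1(1 − p1) + p2(1 − p2))]² / 0.15², with p̄ = 0.675. The two square roots are 0.6624 and 0.6538, and z_β = 0.842.

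| Test | z_α | n per group | with continuity correction |
|---|---|---|---|
| One-sided 5% (as stated) | 1.645 | 120 | 133 |
| Two-sided 5% | 1.960 | 152 | 165 |

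Of these, only the two-sided, continuity-corrected version gives 165. The base of 330 is therefore larger than the stated one-sided test needs (240, or 266 corrected).

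**Step 4: power of 430 analysed children under the stated one-sided test.** Children per group after the design effect: k = 430/(2 × DE). Power = Φ[(0.15 √k − 1.645 × 0.6624)/0.6538]. For the corrected version, 0.15 is replaced by 0.15 − 1/k.

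| m | DE | k | Power | Power, corrected |
|---|---|---|---|---|
| 2 | 1.3 | 165.4 | 90.0% | 87.8% |
| 3 | 1.6 | 134.4 | 84.0% | 80.5% |
| 4 | 1.9 | 113.2 | 78.1% | 73.6% |

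The cluster size at which 430 is just enough is m = 1 + (430/base − 1)/0.3. With the unrounded one-sided requirement of 119.5 per group (base 239) this is 3.7. With the corrected base of 266 it is 3.1.

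**Step 5: error rate if clustering is ignored.** An unadjusted one-sided test at nominal 5% has true error 1 − Φ(1.645/√DE).

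- m = 2: 1 − Φ(1.645/√1.3) = 7.5%
- m = 3: 1 − Φ(1.645/√1.6) = 9.7%
- m = 4: 1 − Φ(1.645/√1.9) = 11.6%

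These figures apply the plan's ICC to a comparison of the two groups at one time point. For a difference in differences the relevant correlation is that of the change within a cluster, which the document does not give.

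**The case against.** **The cluster size is an inference.** The protocol states no m for the design effect and no concession size. Section 8 draws households, for which 2 children is right, and the phrase used in section 5 may simply equate a concession with a household. In a translated document loose wording is as plausible as a wrong calculation. This stands: an arithmetic error is not proven. What remains is that the number and the stated unit agree under only one reading, and the protocol does not say which reading applies.

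**A reader might infer that 430 is too few.** The documents do not support that. The figures of 528 and 627 carry forward a base that exceeds what the stated one-sided test requires. That surplus covers clusters of up to about 3 children, and even at the assumed 4 the power is 74% to 78%.

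**A reader might infer that the plan will produce inflated error rates.** Section 11 is silent on clustering. It does not say that children will be treated as independent, and both difference in differences and the adjusted model can carry cluster-robust errors. A separate analysis plan may add them. This too stands, so the error rates in step 5 are conditional. Even so, section 11 goes as far as naming models, sidedness and software, and leaves out the one feature that section 7 used to enlarge the sample.

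**A reader might treat the milk container as a third randomisation unit.** Section 10.4 attaches the supply rule to the container ("if a herder responsible for the milk container has committed to providing a certain quantity of milk daily to LDB") but says nothing about allocation, and no section equates a container with a concession. The 2 households per container therefore cannot be used to fix the size of a concession.

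**Conclusion.** The concern holds in a limited form. The 430 children rest on 2 per cluster, which is supported only if a concession is one household, and the protocol names two different units for the draw. By its own method the requirement would be 528 or 627 at an assumed 3 or 4 children per cluster. A loss of power below the planned 80% is not established: under the stated one-sided test it appears only above about 3.1 to 3.7 children per cluster, and the actual size is unknown.

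The missing cluster term in section 11 is the more consequential part, because it matters even in the most favourable case. At 2 children per cluster and the plan's ICC of 0.3, a test run as written has a one-sided error near 7.5% in place of 5%. That rests on the assumed ICC being right and on no other document adding the adjustment.

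**What to change.** 1. Use one randomisation unit throughout sections 5, 7 and 8 (and 10.1). If it is the concession, say how many households it holds.
2. In section 7, state the number of eligible children per randomised unit, recompute the design effect with it, and restate the power of 430 children under the test actually planned. Say at the same point whether the 165 per group is one-sided or two-sided, and whether it is continuity-corrected.
3. In section 11.2, state that all child-level analyses use cluster-robust standard errors or random effects at the randomised unit. If a concession can hold several households, apply the same to the household-level analysis of contract fulfilment.

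The cost is a few sentences, a count of eligible children per unit, and a cluster option in the software already named. Intervals will be slightly wider, and the stated power may be less favourable. No extra recruitment is asked for, and the way the lottery is drawn need not change.

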# 8. Conditions of the lottery

The two groups will be chosen by lottery at the first information-sharing meeting. The draw will define the households receiving free fortified Thiakry for all children aged 2 to 5 years within their household (treatment group) and the households not receiving fortified Thiakry during the study (control group), who will receive in kind compensation at the end of the study as thanks for their participation.

